## **Research Protocol**

## **Background:** Resistance training has been described as a “medicine,” as it has the ability to prevent several chronic conditions and contribute to maintaining good health (1,2). Likewise, it is generally understood that resistance training is beneficial for healthy, older, and injured populations. Specifically, it has been shown that resistance training can aid in the development of fitness and maintainence of health, which in turn protects against a number of chronic conditions such as type 2 diabetes mellitus, cardiovascular disease, cancer, and others (2). One potential reason for the benefits of resistance training is the change in body composition that occurs. Although resistance training may reduce fat mass, generally it leads to an addition of skeletal muscle mass (3–5). This addition of muscle is known as hypertrophy. It was well established that muscle hypertrophy occurs following moderate to heavy-load resistance training as well as resistance training to volitional failure using a lighter load (6,7). More recently a novel form of resistance training has emerged as an alternative to heavy-load resistance training. This type of resistance training is known as blood flow restriction training (BFRT) and combines very light loads with the use of a pneumatic cuff placed around the most proximal region of the exercising limb to partially restrict the blood flow (8).

Briefly, BFRT (also known as KAATSU Training for the company that developed it) originated in Japan and has been developed over time since the mid-1900s. Since the 1990s it has undergone rigorous academic research to determine its efficacy as a low-load resistance training alternative. BFRT has been used in a wide range of populations; including elite and high-performance athletes, rehabiliating populations, and elderly adults (9). In essence, BFRT allows for light loads to be used during resistance training by altering the blood flow into the exercising muscles and occluding the blood flow from leaving the muscles, inducing a high degree of metabolic stress which in turn is believed to stimulate muscle adaptation (8,10). Although BFRT is an effective low-load alternative to traditional heavy-load resistance training, there are potential risks with exercise of any kind and BFRT must be undertaken with care to ensure the safety of users. A national survery of KAATSU users in Japan found an extremely low incidence rate for any injuries while doing BFRT (11). Likewise, a number of best-practice guidelines and evidence-based reviews have been published to ensure safe use of BFRT (8,12,13).

The vast majority of studies investigating BFRT include only college-aged males (i.e., between the ages of 18-25) (14). In fact, a call to action in a 2018 review highlights that in studies of chronic and acute (acute meaning one bout of exercise and chronic implying repeated bouts of exercise) BFRT, only 29% and 17%, respectively, of all participants are females (15). This fact necessitates an urgent response. There is no reason for the exclusion of women in BFRT research.

Due to the limited evidence for BFRT with respect to women, the current project aims to provide insight as to how males and females may differ in response to BFRT following six weeks of whole-body resistance training combined with blood flow restriction. Therefore, the objective of this study is to investigate the impact of 6-week, whole-body BFRT on lean body mass, strength, and functional outcomes in males and females with the goal of adding to the growing body of literature, guiding future research on sex differences, and allowing for more specific prescription of this exercise in female populations.

## **Rationale:** There is a substantial gap in the literature surrounding how males and females may be impacted differently following BFRT. Although some studies exist examining sex differences following a BFRT intervention, these studies have investigated outcomes such as electromyography signal (16,17) , muscle fatigue based on torque and maximal voluntary contraction (17,18), metabolic responses (16), and post-exercise application of blood flow restriction (19). No study thus far has investigated whether muscle hypertrophy response following a chronic BFRT intervention differs between the sexes. However, Wells et al. (2019) did observe muscle hypertrophy following a four-week BFRT intervention in a female-only and reported that their findings were similar to previous results observed in males (20). However, no further study has supported or refuted this finding.

While increasing muscle mass might have previously been viewed as an athletic endeavour and weight loss viewed as a health endeavour, but it is now understood that fat mass and muscle mass play independent roles in long-term health and each serve their own purpose. By better understanding the effects of BFRT on lean body mass of males and females, better prescription of exercise can be utilized to maximize lean body mass increases.

## **Objective:** Determine whether any differences in lean body mass or strength are observed between males and females following a six-week whole-body resistance training program with blood flow restriction.

## **Methodology**

### **Study Design:** The current project is a parallel control experimental study comparing men and women following a 6-week resistance training intervention in conjunction with partial blood-flow restriction. (Clinical Trial #: NCT05615831). Briefly, participants will undergo baseline testing separated into two visits within a one-week span, presenting at the Cardiometabolic Exercise and Lifestyle Laboratory at the University of New Brunswick for each visit. Participants will begin six weeks of BFRT within one week of their last baseline testing visit. Following the intervention, participants will undergo follow-up testing at least two days (21), but no more than one week (22), following their last exercise session. All participants will be required to provide written and informed consent prior to participation. The project is being reviewed by the University of New Brunswick Research Ethics Board (REB 2021-124).

###

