### **Sample Size:** A power calculation was performed using G-power software (version 3.1.9.4, Germany) to determine the appropriate sample size for statistical significance. Based on an alpha of 0.05, a power of 0.8, and an effect size of 0.4, we determined the required total sample size to be eight participants for a repeated measures analysis of variance (ANOVA). However, we anticipate a dropout percentage of 13% as reported by Høgsholt et al. (2022) (23). Furthermore, it has been suggested that in order to detect interaction effects between sexes, as well as main effects, the sample size needs to be four-times the size (24). To account for dropout rate, and to ensure adequate ability to detect interaction and main effects, we are attempting to recruit approximately 20 per group for a total of 40 participants.

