### **Primary Outcome Measure:** Lean body mass will be estimated using duel-energy x-ray absorptiometry (DXA) prior to the 6-week BFRT intervention, and again following the intervention. Body composition will be estimated using a Hologic Horizon^®^ DXA System (Hologic Canada ULC, Mississauga, ON, Canada). Lean body mass constitutes that which is not fat mass nor bone mineral mass (42). Participants will present to the laboratory following a 12-hr fast and are asked to refrain from exercise for a 24-hr period prior to testing. Participants will be instructed to wear loose-fitting clothing with no metal (buckles, zippers, buttons, etc.) and then instructed to lie supine on the scanner’s table and remain still for the duration of the scan. Arms will be placed at the participants’ sides with palms facing medially and thumbs pointed upwards. For individuals too large for the width of the table, they will be positioned with one arm outside of the scan area and results of the scanned arm duplicated. The coefficient of variation in our lab for lean mass is 0.6% and for body fat percentage is 0.7%. This was performed on 33 people (males, n=10) with a mean age of 23.4 years and a mean body mass index (BMI) of 25.6.

###

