### **Exploratory Variables:** Anthropometric measurements, muscular power and endurance, and strength will be measured for exploratory purposes and sample description. Participants’ height and weight will be measured to the nearest 0.5 cm and 0.1 kg, respectively, according to the CSEP protocol (43). Weight will be measured using a calibrated column scale (SECA^®^ model #213). Height will be measured using a standardized stadiometer. With no shoes, feet together, and arms at their side, height is taken following an inhalation. Hip and waist circumference are measured using an anthropometric tape measure and recorded to the nearest 0.5 cm. For hip and waist measurements, participants stand with their feet shoulder-width apart and their arms folded across their chest. Waist circumference is measured at the upper lateral border of the iliac crest following a normal exhalation, hip circumference is measured around the widest portion of the buttocks after a normal exhalation (43).

Strength will be assessed by 1-RM for the five exercises used during the intervention. 1-RM will be measured during the second baseline testing visit, at the midpoint of the study during the first exercise session of week four, and again during the second testing visit in the follow-up testing. Each participant’s 1-RM will be determined using the following protocol: one set of 6-10 repetitions, followed by one set of 3-5 repetitions, followed by small incremental increases for one repetition until a failure is achieved within seven attempts. If no failure is achieved within seven attempts, the 1-RM for that exercise will be redone prior to their first exercise session.

Muscular power will be estimated using the squat jump equation derived by Sayers et al. (1999) and is as follows (44):

1. $Peak Power \left( W \right)=60.7 x \left( jump height \left[ cm \right] \right)+45.3 x \left( body mass \left[ kg \right] \right)-2055$

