### **Statistical Analysis:** To test for normality within the sample, Shapiro-Wilk test will be performed and confirmed with a visual examination of the data. General characteristics of the sample will be presented as mean ± SD for continuous variables and n (%) for categorical variables, along with their effect sizes. Effect sizes will be calculated using Hedges *g* formula, which is calculated by dividing the difference between the means by the pooled weighted standard deviation. Differences in baseline and post-intervention values, stratified by sex, will be analyzed using paired sample t-tests. A repeated measures ANOVA will be performed to determine whether there was a significant interaction effect between time and sex with changes in primary and exploratory outcomes. Data management and statistical analyses will be performed using SPSS version 29. A *p* ≤ 0.05 will be considered significant.

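### The Objective ranks strength level with lean body mass while the outcome sections make it exploratory, and one 0.05 threshold serves both: six tests would carry about a 26% chance of a false sex difference if independent, less if positively correlated

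*Protocol*

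**What the plan says.** - **Objective:** the study is to "Determine whether any differences in lean body mass or strength are observed between males and females following a six-week whole-body resistance training program". Lean body mass and strength are joined by a plain *or*, without order.
- **Background, last paragraph:** a broader wording, again unranked: "the objective of this study is to investigate the impact of 6-week, whole-body BFRT on lean body mass, strength, and functional outcomes".
- **Primary Outcome Measure:** a single outcome, "Lean body mass will be estimated using duel-energy x-ray absorptiometry (DXA) prior to the 6-week BFRT intervention", and again afterwards.
- **Exploratory Variables:** "Anthropometric measurements, muscular power and endurance, and strength will be measured for exploratory purposes and sample description". On the measure itself: "Strength will be assessed by 1-RM for the five exercises used during the intervention". No composite and no lead lift is named.
- **Statistical Analysis:** a repeated measures ANOVA looks for a "significant interaction effect between time and sex with changes in primary and exploratory outcomes". One rule closes the section for every test: a p-value "≤ 0.05 will be considered significant".

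**The concern.** Strength is half of the only question in the Objective section, yet the outcome section measures it for exploration and to describe the sample. The two sections give it different standing. The analysis section does not settle the matter, because it sends primary and exploratory outcomes through the same interaction test and calls both significant at the same level.

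The practical risk lies in the write-up. If lean body mass shows no time-by-sex interaction but one of the five lifts reaches 0.05, the Objective lets the authors say that a sex difference in lean body mass or strength was found. The outcome sections say that such a result is only exploratory. The document supports either account, and the choice would be made with the results in view. The error rate of the broader conclusion is then well above the 0.05 that the protocol declares.

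**Working it through.** **What the protocol states.** It gives no family-wise error rate. Its only error figures are the per-test threshold in Statistical Analysis and the single-test inputs in Sample Size ("Based on an alpha of 0.05, a power of 0.8, and an effect size of 0.4"). There is therefore no stated figure to reproduce. The check is what the 0.05 rule implies for the question in the Objective.

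**Inputs**
- Level per test: 0.05 (Statistical Analysis).
- Number of tests: lean body mass (1) plus 1-RM in five exercises (5) = 6. Counting each lift separately is a reading of Exploratory Variables; the protocol does not say it outright.
- Group size for the simulation: 20 per sex (Sample Size).
- Correlation between outcomes: not given, so assumed at 0, 0.3, 0.5, 0.7 and 0.9, equal for all pairs.
- No true sex difference in the change of any of the six outcomes.

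**Independent tests.** The chance of at least one false positive among K tests is 1 − 0.95^K.
- Five lifts: 1 − 0.95^5 = 1 − 0.7738 = 0.226.
- Lean mass plus five lifts: 1 − 0.95^6 = 1 − 0.7351 = 0.265.

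**Limit under any dependence.** K × 0.05 gives 5 × 0.05 = 0.25 for five tests and 6 × 0.05 = 0.30 for six.

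**Correlated tests.** With two time points, the time-by-sex interaction is the same test as a two-sample t-test on the change score. With 20 per sex it has 38 degrees of freedom. Equicorrelated normal change scores were simulated 100,000 times per setting, and a run counted if any test was significant at two-sided 0.05.

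| Assumed correlation | Five lifts | Lean mass + five lifts |
|---|---|---|
| 0 | 22.6% | 26.5% |
| 0.3 | 20.9% | 24.4% |
| 0.5 | 18.3% | 21.1% |
| 0.7 | 15.0% | 16.6% |
| 0.9 | 10.3% | 10.9% |

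The zero-correlation row agrees with the formula. Against the declared 5%, the six-test rate is 26.5/5 = 5.3 times nominal if independent and 10.9/5 = 2.2 times at a correlation of 0.9.

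Strength is also measured at week four. Using three time points would change the form of each strength test but not its 5% level, so the independence figures stand.

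**Effect of an adjustment.** At 0.05/5 = 0.01 per lift, five independent tests give 1 − 0.99^5 = 4.9%.

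**The case against.** **The ranking already exists.** The primary outcome section names one outcome, and the next section labels strength exploratory. This is correct, and it means the lean-mass interaction test keeps its 5% error. A reader might infer that the trial's primary analysis has an error rate near 26%. The documents do not support that: the inflation applies only to the wider conclusion on lean body mass or strength. Unadjusted tests of outcomes presented as exploratory are common practice. That defence is weakened here because the Objective raises strength to a study question.

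**The family of six is a construction.** No section sets a rule under which one significant test meets the Objective, none says that each lift is tested separately, and the Background wording would give a wider family. All true. Six is the count that follows from the Objective section and the five lifts when no other strength variable is defined.

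**26% might be read as a ceiling, or as the rate for the lifts alone.** It is neither. It is the independence value for six tests. The limit under any dependence is 30%, positive correlation brings the rate below 26%, and five lifts alone give 23% if independent.

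**A strength composite or a multiplicity rule may sit in a statistical analysis plan.** That is fair, and their absence here is not the point. The point is the conflict between the Objective and the outcome sections, together with the single threshold, all of which are in the protocol.

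**Conclusion.** The concern holds as an internal contradiction in the protocol together with a significance rule that does not protect the stated Objective. If there is no true sex difference in any outcome and each lift is tested separately, the chance of at least one false sex difference is about 26% with independent tests. It falls to between 24% and 11% over assumed correlations of 0.3 to 0.9. The correlations are assumptions, since the protocol gives none. The contradiction itself depends on neither the correlations nor the count of six. Because the primary test remains valid, this is a point that should be corrected rather than one that undermines the design.

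**What to change.** 1. **Objective (and the matching sentence in Background):** bring it into line with the outcome sections. State that the time-by-sex test on lean body mass is the single confirmatory test and that strength and functional outcomes are exploratory.
2. **Statistical Analysis:** restrict the 0.05 significance claim to the lean-mass interaction. State that strength and the other exploratory outcomes are reported as estimates with 95% confidence intervals and carry no confirmatory claim.
3. **If strength is to support a conclusion on sex differences:** say so, and apply Holm across the five lifts, with the smallest p-value compared against 0.05/5 = 0.01. This holds the strength claim at 5%, separately from the lean-mass test. If the combined conclusion on lean body mass or strength is itself to be held at 5%, the adjustment has to cover all six tests, starting at 0.05/6 = 0.0083. A single pre-specified strength summary is another option but not a requirement; it would be a new endpoint on which statisticians could differ.

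**Cost:** wording in two or three places and no new data. A p-value on a single lift could no longer carry the headline, and Holm would cost some power for each lift.

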### **Sample Size:** A power calculation was performed using G-power software (version 3.1.9.4, Germany) to determine the appropriate sample size for statistical significance. Based on an alpha of 0.05, a power of 0.8, and an effect size of 0.4, we determined the required total sample size to be eight participants for a repeated measures analysis of variance (ANOVA). However, we anticipate a dropout percentage of 13% as reported by Høgsholt et al. (2022) (23). Furthermore, it has been suggested that in order to detect interaction effects between sexes, as well as main effects, the sample size needs to be four-times the size (24). To account for dropout rate, and to ensure adequate ability to detect interaction and main effects, we are attempting to recruit approximately 20 per group for a total of 40 participants.

### **Participation**

#### **Inclusion Criteria:** Participants will be eligible for inclusion if they are between the ages of 19 and 30 years. In addition, participants need to be physically inactive, but otherwise healthy. Physical inactivity is defined as not meeting the World Health Organization’s 2020 physical activity guidelines: 150 minutes of moderate-vigorous physical activity and two muscle-strengthening activities per week (25). Physical activity levels will be estimated through questionnaires and using Fitbit Charge 3 activity trackers. It was shown in a 2018 systematic review that Fitbit activity trackers provide accurate measures of steps in adults with no mobility limitations (26). Using a pre-determined threshold (10,000 steps/day) as the minimum number of steps required to reach moderate intensity physical activity, anybody who averages under 10,000 steps/day over a 4–7-day window and does not perform muscle strengthening activities twice per week will be considered physically inactive (27).

#### **Exclusion Criteria:** Exclusion criteria includes: 1) aged outside prearranged threshold (19 – 30 years), 2) the presence of cardiovascular disease such as coronary heart disease, uncontrolled hypertension, peripheral vascular disease, venous thromboembolism, other blood clotting disorders, or hemophilia, 3) surgery, bone fracture, or a skin graft within the last three months, 4) pregnancy, and 5) meeting or exceeding physical activity guidelines.

#### **Recruitment:** Recruitment will be performed between May 2022 and July 2023 through the distribution of promotional flyers, University of New Brunswick’s newsletter, and social media advertisements through Facebook and Instagram.

### **Exposure Variable – Blood Flow Restriction Training:** Participants will undertake 6 weeks of whole-body resistance training in conjunction with blood flow restriction to their exercising limbs. The intervention consists of three supervised exercise sessions per week consisting of five different exercises: knee flexion (hamstring curl), knee extension, leg press, chest press, and seated row. The exercise load will be individualized to 30% of each participant’s 1-RM for each exercise. Participants are required to complete 75 total repetitions broken into four sets for each exercise. The sets are broken up in the following manner: set 1: 30 repetitions; set 2: 15 repetitions; set 3: 15 repetitions; set 4: 15 repetitions, as this protocol has previously been used in blood flow restriction research to induce muscle hypertrophy in a variety of populations (28,29) and has been suggested by multiple reviews (13,30). At week 4, participants will have their 1-RM reassessed to adjust the 30% 1-RM exercising loads. This will occur during the first exercise session of Week 4. As such, following the 1-RM reassessment, participants will perform two sets per exercise (30 reps and 15 reps) using the newly adjusted 30% 1-RM weight, before returning to the original rep scheme for their next session.

Blood flow restriction cuffs will be placed at the most proximal portion of the exercising limb (just above biceps brachii on the arm and near the inguinal crease on the thigh), which has previously been used in BFRT research (8,13,28,29,31–34). Blood flow restriction was achieved using the KAATSU C3 device (KAATSU Global, Inc., Huntington Beach, CA, USA). The KAATSU arm and leg cuffs are 5 cm wide, respectively, and are single-bladder cuffs. Cuffs will be inflated to 60% of each individual’s total limb occlusion pressure as this has been shown to be a safe and effective pressure to induce muscular adaptations (35), and is within the recommended pressure range for BFRT (8,13). Each participant’s total limb occlusion pressure (LOP) will be estimated using equations developed by Loenneke et al. (2015) listed here (31):

1. $Leg arterial occlusion \left( mmHg \right)=5.893\left( thigh circumference \right)+0.734(diastolic blood pressure)+0.912(systolic blood pressure)-220.046$
2. $Arm arterial occlusion \left( mmHg \right)=0.514\left( systolic blood pressure \right)+0.339\left( diastolic blood pressure \right)+1.461\left( arm circumference \right)+17.236$

Although these equations have modest R-squared values of 0.61 and 0.49, respectively, they have been successfully utilized in a BFRT intervention of trained athletes leading to significant improvements in muscle hypertrophy and functional outcomes with no reported side effects (36). Furthermore, although LOP will be estimated, a study comparing the impact of various cuff pressures showed similar effects on muscle size, torque, strength, and endurance between 40% and 90% pressures (37). These findings suggest that greater pressures are not necessarily more effective at inducing adaptations and that small pressure fluctuations will not necessarily serve as greater or lesser stimuli during training. Cuffs will remain inflated during the rest in between sets of each exercise but will be deflated for the rest period between exercises (28,38–41). The set rest is 60 seconds, and the rest between exercises is four minutes.

